### Participant recruitment {15}

Prior to the recruitment procedure, we hosted a meeting with heads of villages, administrative staff from community-based eldercare centers, and representatives from social work organizations on October, 2020. We first explained the aims and target population of this eldercare model to each attendee. Then the healthcare program was introduced including adopted therapies, frequency of rehabilitation services, and follow-up visits. After addressing their questions, they were encouraged to spread the information. Brochures regarding this eldercare model were also given to them. The coordinator team, enrolled in the study, will select eligible participants from the roster that includes residents over 65 years old provided by the county government in each CEC. We used roster as it is the most complete, comprehensive, and accessible pool of older residents in Lishui county. Information sessions organized by research team will be held at a convenient time in each CEC for service providers. The coordinator team will then contact eligible individuals to discuss the CIE intervention and study requirements, inviting them to provide informed consent for inclusion in the study.

Participation in this study is voluntary. Eligible residents will be reassured that the decision not to be involved in the study would not have any impact on their current or future access to geriatric or primary healthcare services. There is no anticipated harm and compensation for trial participation. For residents who participated in this study, post-trial care is not available.

### Randomization and blinding {16a,16b, 16c, 17a}

Community eldercare centers (CECs, clusters) are recruited, and then they are allocated to different steps using computer-generated random numbers. The random-sequence remains concealed from all stakeholders during the first 6 weeks of the study so that all sites start usual care blinded of when the CIE model will start. Then an independent biostatistician discloses to the principal investigator which five sites have been randomized to start the CIE model in the first step. Each site is simply informed 2 weeks prior to each site starting to recruit residents. The five sites undergo a transition phase of 2 weeks with training and coordination before crossing to the intervention phase. All other sites continue usual care, still blinded on which time the CIE model will be offered, until the last 2 weeks before the next step. We do not anticipate any requirement for unblinding, but if required, the enablement officer, coordinator team, multidisciplinary team, and advisory committee will have access to group allocations and any unblinding will be reported.

Since blinding is not possible for trial participants and care providers in such a stepped-wedge design where all participants receive interventions sequentially, several procedures are used to minimize contamination and bias. First, clusters are geographically dispersed. Second, data collection staff is separate from the intervention team and blind to the on-going intervention study. Data analysts will not be aware of the identification information on participating CECs and individuals.

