**Methods:**

CIE is a prospective stepped-wedge cluster randomized trial conducted at 5 community eldercare centers in rural China. The multifaceted CIE intervention, guided by chronic care model and integrated care model, consists of five components: comprehensive geriatric assessment, individualized care planning, community-based rehabilitation, interdisciplinary case management, and care coordination. The intervention is rolled out in a staggered manner in these clusters of centers at an interval of 1 month. The primary outcomes include functional status, quality of life, and social support. Process evaluation will also be conducted. Generalized linear mixed model is employed for binary outcomes.

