### Study sites and participants {10}

Five CECs were purposively selected based on geographic location and representativeness of the frailty in Lishui county.

Study sites were purposively selected in collaboration with villagers committee and Bureau of Civil Affairs according to the following criteria: (1) sites where CBR services were delivered by the tertiary hospital; (2) at least 20,000 visits per year altogether in selected CECs. Based on previous data in the county [17], we assumed each site may be able to see on average 40 frail older people and they are present at least 100 days per year (eight per month); (3) routine eldercare available onsite; (4) no previous introduction of interventions/organizations for integration or increasing services, apart from CIE that is considered as standard-of-care throughout the whole study period.

Study participants consists of all the adults aged 65 or older who are present for care in the selected CECs and agree to participate during the study period. Inclusion criteria are as follows: (1) with household registration in Lishui county; (2) not planning to move away from Lishui county in the prospective follow-up of the study; (3) Chinese version of Mini-Mental State Examination score ≥ 20; (4) written informed consent to participate in the study. For those who had difficulty in writing, informed consent was obtained from their spouses/children. The oral informed consent was recorded when the older people or their family members cannot write. Exclusion criteria are as follows: (1) on a waiting list for a nursing home; (2) with a terminal medical condition; (3) older adults who have psychiatric disorders or other illnesses that require hospitalization; (4) older adults who are currently receiving specialist geriatrician intervention and/or care coordination.

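### The randomisation section starts all five centres in the first step, contradicting the staggered design, and its recruitment sentence conflicts with the trial's own timetable

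*Protocol article*

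**What the plan says.** All references are to the protocol article.

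**Number of centres.** The abstract (Methods) states "CIE is a prospective stepped-wedge cluster randomized trial conducted at 5 community eldercare centers in rural China". *Study sites and participants* agrees: "Five CECs were purposively selected based on geographic location and representativeness of the frailty in Lishui county". The caption of Fig. 1 also gives five clusters.

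**Roll-out.** The abstract says that the intervention is "rolled out in a staggered manner in these clusters of centers at an interval of 1 month". *Randomization and blinding* says that the centres are recruited and "then they are allocated to different steps using computer-generated random numbers". A few lines later it says that an independent biostatistician "discloses to the principal investigator which five sites have been randomized to start the CIE model in the first step". It then describes five sites going through a two-week transition, while all others stay in usual care until the next step.

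**Measurement.** *Outcomes* gives four times: T0 at week 2, T1 at week 6 (end of observation), T2 at week 28 (20 weeks after the intervention begins) and T3 at week 48. *Study design* specifies repeated cross-sectional samples, and *Sample size* counts individuals per cluster per period.

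**Recruitment.** *Randomization and blinding* conceals the sequence for the first 6 weeks and adds: "Each site is simply informed 2 weeks prior to each site starting to recruit residents". *Participant recruitment* says: "The coordinator team, enrolled in the study, will select eligible participants from the roster". The *Procedure* subsection has the same team coordinating care under the model. *Trial status* places recruitment in October to about November 2022.

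**The concern.** The statements on roll-out cannot all be carried out. If five of five centres start in the first step, none is left to wait, and the number appears twice in the section (for disclosure and for transition). The *Outcomes* timetable does not correct it, because it is written as if there were one start date.

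A stepped wedge separates the intervention from calendar time only because, at some times, some clusters have crossed and others have not. Without that overlap the study is a before-after comparison, exposed to the secular trends that the *Discussion* itself lists as a challenge.

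The recruitment sentence raises a second issue. Read literally, a site hears that its turn is coming and then starts recruiting. The people who choose from the roster also coordinate the intervention, so they could approach different residents once they know. The listed safeguards (dispersed clusters, separate data collectors, analysts unaware of identities) do not act on enrolment.

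**Working it through.** **Plan's own figures.** The point disputes no figure. The minimum cluster size of 76 cannot be reproduced, because *Sample size* gives no effect size, SD or number of periods. The step to 92 follows from 76 × 1.2 = 91.2, rounded up. I take 76 and 92 per cluster per period and the ICC of 0.01 as given.

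**1. Sites left in usual care after step 1.** 5 − 5 = 0.

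**2. Is the effect estimable?** The Hussey and Hughes model has one fixed effect per period, one treatment effect and a random cluster effect. The treatment effect is estimable only if its column is not a sum of period columns. The article does not state six periods or one centre per step; I assume both for the staggered layout.

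| Layout (5 centres) | Rank / columns | Treatment effect |
|---|---|---|
| All five in step 1, 6 periods | 6 of 7 | not estimable (treatment = periods 2 to 6) |
| One centre per step, 6 periods | 7 of 7 | SE 0.070 SD at n = 76; 0.065 SD at n = 92 |

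With total variance 1, 80% power and two-sided 5%, the detectable effect in the second layout is (1.96 + 0.84) × SE, which is 0.197 SD at 76 and 0.181 SD at 92.

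**3. Measurement weeks.** The implied start is 28 − 20 = week 8, which equals 6 weeks of concealment plus 2 weeks of transition. Monthly starts (4 weeks) fall at weeks 8, 12, 16, 20 and 24. With T0 to T3 at common weeks 2, 6, 28 and 48, every centre has the exposure pattern 0, 0, 1, 1. The rank is 4 of 5, so the effect is again not estimable. With a month of 4.345 weeks the last start is week 25.4, still before week 28.

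Counting the weeks on each centre's own clock (shifts of 0, 4, 8, 12 and 16 weeks) does not help. Control measurements would run from week 2 to week 22 (6 + 16) and intervention measurements from week 28 to week 64 (48 + 16). They never overlap (rank 16 of 17 with calendar-week effects), and week 64 lies beyond the 48 weeks in *Study design*.

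**4. What an analysis without period effects would do.** With two control and two intervention measurements in five centres and n = 76, the SE is √[(0.99/76) × (1/10 + 1/10)] = 0.051 SD. With no true effect, an assumed secular shift of 0.05, 0.10 or 0.15 SD would be declared significant about 17%, 50% or 84% of the time. The shifts are assumptions, not figures from the article.

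**5. Recruitment timing.**
- T0 at week 2 and T1 at week 6 both need participants while the sequence is concealed.
- A recruitment window of about two months at the start points the same way.
- The sentence on informing sites before they recruit points the other way.
- Repeated cross-sections, with sample size counted per period, imply that some sampling comes later.

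The article does not settle which participants are selected before disclosure and which after.

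**The case against.** A reader might infer that the trial has no wedge and that nothing is randomised. The documents do not support this. The same section allocates centres at random to different steps and keeps other sites in usual care until the next step. The abstract gives a one-month stagger, and the *Discussion* describes roll-out at different time points. Fig. 1, not available here, may show the intended layout. The likeliest explanation is a wrong count. That stands, and it makes this a contradiction to reconcile, not a proven absence of a wedge. It does not dispose of the point: the count appears twice, the *Outcomes* timetable fits a single start, and correcting the count alone would leave the measurement problem.

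A reader might also infer that all recruitment follows disclosure. T0, T1 and the recruitment window suggest that much of it falls inside the concealed period, where concealment does protect it. The sentence also does not say exactly what sites are told. Eligibility covers all consenting adults aged 65 or older who attend and meet the criteria, and the roster comes from the county government; both narrow the recruiters' discretion without removing it. The selection risk is therefore conditional, and nothing in the article allows its size to be estimated.

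The SE and detectable effect for the staggered layout rest on six measured periods and one centre per step. Neither is stated, and only four measurement times are.

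**Conclusion.** The point holds as an internal contradiction that must be resolved before the plan can be followed. The site count in *Randomization and blinding* conflicts with the rest of that section and with the abstract. Read literally, it leaves no site in usual care after step 1 and no estimable treatment effect in the planned model. The measurement weeks in *Outcomes*, taken as common calendar weeks, have the same effect even with monthly staggered starts. These rank results need only the exposure patterns, not the ICC or sample size; they assume categorical period effects, as in the Hussey and Hughes model, and monthly steps from week 8.

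The recruitment sentence conflicts with T0, the 6-week concealment and the recruitment window. Selection bias is a risk for whatever part of recruitment follows disclosure; that part is unknown, and no size is claimed.

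**What to change.** 1. In *Randomization and blinding*, correct the number of sites per step to match the staggered design and Fig. 1 (one site per step if five sequences are intended). State that only the next site or sites are disclosed at each step.
2. In *Outcomes*, restate the schedule so that every centre is measured at each step or period, giving times when crossed and uncrossed centres are both observed.
3. Reconcile the sentence on informing sites before recruitment with *Study design*, *Outcomes* and *Trial status*. Say which samples are drawn before disclosure and which after.
4. For cross-sectional samples drawn after disclosure, have the independent biostatistician draw each site's ordered contact list from the roster for each period, so that the coordinator team does not choose whom to approach.

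Completing all recruitment before disclosure is not proposed, because it would conflict with the repeated cross-sectional design.

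Cost: items 1 and 3 are wording. Item 2 may add measurement rounds, since only four times are now listed. Item 4 adds a little work for the biostatistician.

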### Data collection, management, and monitoring {18a, 18b, 19}

Trained external assessors are responsible for the collection and maintenance of study records and data using web-based data collection and storage programs along with mobile tools such as an iPad and/or cell phone.

At the study center in Lishui, data will be entered electronically into a database. ^**{27}**^All information of the participants will be kept confidential using an identification code for each participant. During the electronic recording, a designated data entry person is trained for data plausibility to avoid erroneous data entry. Data will be entered within 1 month after each measurement point. After freezing the data, any further changes to the database will be impossible. For quality assurance, all entered data will be shared with a biostatistician via a password-protected file storage server by the principle investigator on a monthly basis. The biostatistician will collate the data, review data quality in terms of numbers, consistency, and completeness^**{21b,29}**^. A data monitoring committee was not considered as this was a low-risk intervention.

An advisory committee consisting of one principal investigator, one enablement officer, and three experts (medical ethics, social science, and public health) randomly selected from think tank by the county government will be formed to monitor the implementation and research. The committee checks with the onsite coordinator team on the status of implementation of the model at least every 3 months. A short-form report is filled out to be submitted to the research team^{5d,11c,21a,23}^.

### Statistical analysis {20a, 20b, 20c}

Data analysis will be performed using STATA 15. Baseline differences between clusters will be tested using Pearson’s chi-square statistic and ANOVA.

Statistical analysis is based on the Hussey and Hughes model for the analysis of cross-sectional SW-RCT designs [37]. Generalized linear mixed models (GLMM) will be used to determine the effect of the CIE model on the primary outcomes. Two random effects will be introduced, one at the cluster (eldercare centers) level and the other at the individual (frail older people) level. In addition to assessing the intervention effect, we will also investigate whether the time of intervention impacts the effectiveness of the intervention by adding an interaction term between time and intervention as a fixed effect. A secondary analysis will be conducted to adjust for baseline covariates to account for potential confounding effects. The same GLMM will be used to model the primary outcomes. Estimates of difference and 95% CIs will be calculated.

Qualitative data from interviews or focus groups will be analyzed using content analysis, document analysis, etc.

The analysis is based on intention to treat (ITT) principle. Multivariable normal models will be used for imputation of missing values to enable ITT analysis. A *P* value < 0.05 will be considered statistically significant.

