## Methods

### Study design {8}

This study will adopt a multicenter, prospective, unidirectional randomized controlled trial using a stepped-wedge cluster design with repeated cross-sectional samples. Four phases will be sequentially rolled out over 48 weeks: preparation, control phase (standard care exposure), transition phase (intervention introduction), and intervention exposure (Fig. 1).

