### Sample size {14}

The sample size for this stepped-wedge controlled randomized trial (SW-CRT) is calculated to detect minimal significant effects on the variable of quality of life: accepting an alpha risk of 0.05 and a beta risk of 0.20 in a bilateral contrast, referring the study of Ana.et al. [34]. Assuming the intracluster correlation coefficient (ICC) to be 0.01 based on Boorsma et al.’s study [35] and correlation coefficient to be 0.25 based on the ratio between the ICC and the correlation coefficient used in the study of Muntinga et al. [36], a minimum cluster size of 76 individuals is required to detect the expected intervention effect with 80% power at the 5% significance level.

Based on our earlier survey study on community-dwelling older people and available data on the characteristics of long-term care residents [17], we expect a 20% loss to follow-up due to mortality, impossibility, or unwillingness to participate further, 16 more individuals would be required, the resultant sample size is determinate in 92 individuals per cluster per period.

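### Under the stated cross-sectional sampling, a short set of entry covariates would serve better in the primary model than in a secondary analysis; a cheap improvement, not an error.

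*Protocol article*

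**What the plan says.** In the protocol article, Statistical analysis {20a, 20b, 20c} rests the analysis of the primary outcomes on the Hussey and Hughes model, fitted as a mixed model with a random effect for centre and another for the individual. No baseline covariates are named for it. They enter afterwards: "A secondary analysis will be conducted to adjust for baseline covariates to account for potential confounding effects". The same section states that "Baseline differences between clusters will be tested" with chi-square and ANOVA, but does not say that these tests will choose covariates.

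Other places bear on this:

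- Study design {8} describes a "stepped-wedge cluster design with repeated cross-sectional samples".
- Study sites and participants {10}: "Five CECs were purposively selected based on geographic location and representativeness of the frailty in Lishui county". It also makes age and a minimum Mini-Mental score conditions of entry.
- Participant recruitment {15} has the coordinator team pick eligible people from a roster and invite them.
- Randomization and blinding {16a, 16b, 16c, 17a} randomizes centres to steps, tells each site two weeks before it starts to recruit, and states that participants and care providers cannot be blinded.
- The Discussion lists secular trends and effect heterogeneity as sources of confounding, and names adjustment for baseline covariates among the remedies to be put in the statistical analysis plan.

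**The concern.** With repeated cross-sectional samples, the people measured before and after a centre crosses over need not be the same. A random effect for the individual then cannot remove differences between them, and prognostic differences stay in the residual variance of the primary estimate.

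Bias is also possible. The coordinator team, made up of a GP and a community staff member (Procedure), chooses whom to approach from the roster and may know by then that its centre is about to cross over. If the people approached differ from those approached earlier, case mix changes within the centre at the same moment as exposure. Centre and period effects do not absorb that. Measured individual covariates remove the part they explain.

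At stake are some precision and some protection for the headline estimate. Both are available at no recruitment cost, and the protocol itself names the tool that would supply them.

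**Working it through.** **Inputs from the document** (Sample size {14}): "accepting an alpha risk of 0.05 and a beta risk of 0.20 in a bilateral contrast"; "Assuming the intracluster correlation coefficient (ICC) to be 0.01"; and "a minimum cluster size of 76 individuals is required to detect the expected intervention effect with 80% power". A second coefficient is given without its type: "correlation coefficient to be 0.25 based on the ratio between the ICC and the correlation coefficient".

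**The plan's own figure.** The 76 cannot be reproduced, because no effect size or standard deviation is stated. The standardized effect that it implies can be solved for instead.

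**Assumptions.** Five centres, six periods, one centre crossing per step; total variance 1; normal approximation. The article does not fix this layout (Outcomes {12} gives four measurement times). The share R² of individual variance that covariates explain is also assumed.

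**Formula** (Hussey and Hughes), with I = 5, T = 6, τ² = 0.01 and σ² = 0.99(1 − R²)/76:

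Var = Iσ²(σ² + Tτ²) / [(IU − W)σ² + (U² + ITU − TW − IV)τ²]

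- U, all exposed cells: 1+2+3+4+5 = 15.
- W, squared period totals: 0+1+4+9+16+25 = 55.
- V, squared centre totals: 25+16+9+4+1 = 55.
- IU − W = 75 − 55 = 20.
- U² + ITU − TW − IV = 225 + 450 − 330 − 275 = 70.

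**Unadjusted (R² = 0).** σ² = 0.99/76 = 0.01303. Var = 5 × 0.01303 × 0.07303 / (20 × 0.01303 + 0.70) = 0.00495, so SE = 0.0704. The effect detectable with 80% power is (1.960 + 0.842) × 0.0704 = 0.197 SD.

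**Adjusted**, holding that 0.197 SD effect fixed:

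| R² (assumed) | SE ratio | Cut in variance | Power |
|---|---|---|---|
| 0.02 | 0.991 | 2% | 81% |
| 0.05 | 0.977 | 5% | 82% |
| 0.10 | 0.953 | 9% | 84% |
| 0.20 | 0.903 | 18% | 87% |
| 0.30 | 0.849 | 28% | 91% |

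**Other readings.**

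- If 0.25 is a cluster autocorrelation, R² of 0.1, 0.2 or 0.3 cuts the variance by 6%, 11% or 17%, and power becomes 82%, 84% or 87%.
- If the same people are re-measured and the individual random effect is in the model (assumed individual autocorrelation 0.25 to 0.7), the cut is 0.2% to 2.4% and power is 80% to 81%.

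**Stable centre differences.** At ICC 0.01 and 76 per cell, a fixed difference at a centre enters the effect estimate with weights +0.136, +0.068, 0, −0.068 and −0.136 by step order. An extreme contrast (first centre +0.2 SD, last −0.2 SD) gives 0.2 × 0.136 + 0.2 × 0.136 = 0.054 SD. At ICC 0.05 it is 0.013 SD, and at ICC 0.10 it is 0.007 SD.

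**Case mix that changes with exposure.** A shift of 0.1 SD at crossover in every centre passes through in full: 0.10 SD, against 0.197 SD detectable.

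**The case against.** The strongest reply is that nothing here is wrong. An unadjusted primary model with a planned adjusted analysis beside it is an accepted convention, and the Discussion defers the handling of confounding to a statistical analysis plan that is not shown. That stands, and it sets the weight of the point.

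The sampling scheme is also uncertain. The individual random effect, the allowance for loss to follow-up, and a recruitment window of about October to November 2022 (Trial status) all suggest that the same people are followed. If so, the precision gain almost vanishes, and so does most of the scope for recruitment to change at crossover. This also stands. The point therefore rests on the cross-sectional design as stated.

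The size of R² has no source in the document, and age with a Mini-Mental score restricted to 20 or above may explain little of quality of life. Hence the low end of the table.

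A reader might infer that purposive choice of five centres exposes the primary estimate to their case-mix differences. The documents do not support that. Purposive choice bears mainly on generalizability; step order is randomized, each centre contributes both control and intervention time, and the leak computed above is small to modest. A reader might also infer that the baseline tests between centres will select covariates, which the article does not say. Nor does it show that any shift in recruitment will occur. It only leaves room for one.

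**Conclusion.** The point holds as a low-cost improvement, not as the correction of an error or contradiction. Under the stated repeated cross-sectional design and the assumed 5 by 6 layout, moving individual covariates into the primary model lowers the standard error by roughly 1 to 2% with weak covariates and 5 to 15% with moderately strong ones. It also gives partial protection against a within-centre change in case mix at crossover, limited to what the covariates measure.

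Calling the gain free would go slightly too far. With a non-identity link, as for any outcome analysed as binary, adjustment changes the conditional effect being estimated. Adjustment also does not repair other problems of design. In particular, if the four measurement times are common calendar times and every centre crosses between weeks 6 and 28, exposure cannot be separated from time whatever covariates are added.

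**What to change.** In Statistical analysis, make the primary mixed model adjust for a short, prespecified set of individual-level covariates recorded at entry: age, Mini-Mental score, and sex if it is recorded (the article does not say that it is). Report the unadjusted model as the sensitivity analysis. Do not add the T0 value of the outcome as a covariate while T0 also serves as one of the four outcome measurements; people sampled later would not have it in any case. Keep to individual-level covariates, since centre-level ones would use up the few degrees of freedom that five centres provide. For any outcome analysed as binary, label the adjusted result as a conditional effect given the covariates.

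The cost is wording only. Age and Mini-Mental score are already needed to establish eligibility. It would help to state at the same time whether the same people are re-measured, because the size of the gain depends on that.
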